### Timeline

Recruitment began in June 2015; the intervention period ends in April 2018. Figure 2 shows the study schedule of enrollment, intervention, and assessments.

**Fig. 2 Fig2:**
[figure not shown]
Study schedule of enrolment, intervention, and assessments

### Statistical analysis

#### Missing data

Participants complete their intake and enrollment interviews before randomization. Based on past experience, we expect to complete 90% or more of the 3- and 6-month post-enrollment interviews and have less than 1% missing data on core items. Multiple imputations will be used to replace missing data to allow the least biased estimate for each analysis [76]. To further reduce potential bias, analyses will be rechecked by running them without missing data. If differences result, a general latent variable framework [77] will be used to analyze non-ignorable or systematic missingness that tests whether missing data are qualitatively different by condition.

#### Analysis for aims 1 and 2

We will evaluate the effects of EMAs, EMIs, and EMAs + EMIs on the days of abstinence (H1) and HIV risk behaviors (H2) measured from enrollment to 6 months after enrollment using multilevel structural equation modeling (MSEM) with mixed effects in MPlus (version 6.1). The analysis will model observations (level 1) nested within participants (level 2), with participants modeled as a random factor. Random assignment to the four groups will be modeled as a level 2 predictor in the 2 × 2 factorial design [78] with the three planned orthogonal contrasts shown earlier in Table 1. To be conservative, a Bonferroni correction for family wise error (*p* = 05/3 = 0.017) will be used on primary outcome (days of abstinence) in the three a-priori hypothesis tests for the effect of getting EMA or not (H1a), EMI or not (H1b), and their interaction (H1c). As noted earlier, self-monitoring via EMAs is expected to change behavior. Based on the preliminary studies, we expect EMIs to have an effect in their own right and for the combined EMA + EMI condition to have an additional effect (i.e., an interaction). This and all analyses will use an intent-to-treat approach (i.e., participants are analyzed as assigned regardless of their actual level of participation). Prerandomization participant characteristics, severity, and treatment experience used for urn randomization will be checked for any group differences and used in a propensity score covariate to further reduce unexplained variance. Restricted maximum likelihood estimation (REML) will be used within condition to allow the use of all available data. If there is a significant effect for H1 or H2, we will also examine all six of the possible pairwise comparisons, using an experiment-wise error of .05 and a pairwise test alpha of .05/6 tests = .0083.

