### Sample size

For the primary outcome (H1) power analysis, we assumed a sample size of 400 with treatment intake records/services data from the provider (for covariates), interviews by research staff at three time points for the main analysis (baseline and 3 and 6 months), a completion rate of 90 + % per wave of 100 participants, a moderate effect size of Cohen’s *d* = .4 based on Cox’s formula [71] for converting the odds ratio from a pilot study to effect size *d* = LN(1.9)/1.65 = .4)), a target of at least 90% power with a family wise alpha of < .017 on the three a-priori orthogonal contrasts testing the hypothesized effects of EMA, EMI, and their interaction on the primary outcome (days of abstinence), and at least 80% power for all six pairwise comparisons with a family wise alpha of < .0083. The effective *n* for power calculations in repeated measures analysis varies between a lower bound of the number of unique people (*N* = 400 people) and an upper bound of observations from baseline and completed follow-up or 1120 observations (O = (400 people + 90% × 400 people × 2 follow-ups) = 1120) as a function of the Intraclass Correlation Coefficient (ICC) associated with the individual and the number of repeated measures (RM) per person (effective *n*’ = O/(1 + ICC(RM − 1)). In prior samples from the proposed recruitment site [6], the ICC of the days of abstinence between enrollment, 3, and 6 months post enrollment was .52, resulting in an effective *n*’ of 549 (*n*’ = 1120/(1 + .52(3 − 1)) = 549) and 98% power for a two-tailed test of *p* < .017. Note that in the special case of a balanced 2 × 2 as proposed here, the power for the interaction test is the same as each of the main effects [71–74]. In the same study, the ICC of the HIV Risk Behavior Scale was .51, resulting in an effective *n*’ of 554 and 99% power for a two-tailed test of alpha < .05. For the six possible pairwise comparisons, the effective sample size (*n*’ = 275 per pair for H1 and H2) will be sufficient to have 80% power for a two-tailed test of *p* < .0083. Following the recommendations of Piantadosi [75], we have powered this design for the most conservative pairwise tests so that we can look at the efficacy of each combination (EMA, EMI, EMA + EMI) relative to the control and their comparative effectiveness with each other. For mediation analysis (H3), the tests should have 90% + power for a two-tailed test of *p* < .05 for an indirect effect size of *d* = .22 or more.

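### The non-ignorable missing-data analysis depends on imputed and complete-case results differing, a trigger with no reliable or specific power to detect outcome-dependent loss

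*Protocol article*

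**What the plan says.** The protocol article, under Missing data, sets out three steps. Missing values are multiply imputed. Then "analyses will be rechecked by running them without missing data", which I read as a complete-case analysis. The third step is conditional: "If differences result, a general latent variable framework [77] will be used to analyze non-ignorable or systematic missingness". That last analysis is described as one that "tests whether missing data are qualitatively different by condition". The article does not say how large a difference counts.

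The same section states that "we expect to complete 90% or more of the 3- and 6-month post-enrollment interviews". Under Analysis for aims 1 and 2, the main model is fitted as follows: "Restricted maximum likelihood estimation (REML) will be used within condition to allow the use of all available data". No section of the article plans a non-ignorable analysis that runs regardless of the comparison.

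**The concern.** No non-ignorable imputation model is described, so I take the imputation as the standard kind, which assumes that data are missing at random given what was observed. Complete-case analysis needs a stricter condition, but it too uses only observed values. If people who relapse miss the visit, and their observed history does not fully predict it, both estimates shift together and the condition is not met. If loss depends on an earlier observed outcome, the two can differ although imputation is already valid. The REML model also relies on ignorability, so it offers no independent check.

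The primary outcome is days of abstinence, self-reported for the last 90 days, and follow-up surveys are completed at office visits. Relapse can plausibly affect both the outcome and attendance. Under the stated rule, the primary result could pass the planned recheck while the assumption most open to doubt goes unexamined.

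**Working it through.** **The plan's own figure.** The 90% completion rate enters the sample size calculation. Observations: 400 + .9 × 400 × 2 = 1120. Effective n′ = 1120 / (1 + .52 × 2) = 549, as stated. Power at two-sided .017 is 98.9% with d = .4, or 98.5% with the unrounded ln(1.9)/1.65 = .389. The article states 98%. These figures reproduce and the present point does not alter them.

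**Size of bias.** Let m be the fraction missing in an arm and δ the amount, in SD, by which non-completers are worse than imputed. The arm mean is then too high by m × δ. Assume m = .15 for control and .05 for each other arm, with δ from .5 to 1.0. These values are assumptions. They imply 7.5% loss overall, which is inside the 90% expectation overall but not in the control arm.

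- One arm versus control: (.05 − .15) × δ = −.10δ, so −.05 to −.10 SD. Against d = .4 this is 12.5 to 25%, toward the null.
- EMA or not (and likewise EMI or not): (.05 + .05)/2 − (.15 + .05)/2 = −.05, so −.025 to −.05 SD. This is 6.25 to 12.5% of .4, toward the null.
- Interaction, as half the difference of differences: ½[(.05 − .05) − (.05 − .15)] = +.05, so +.025 to +.05 SD. The size is the same but the direction is upward.
- Equal 10% loss, with δ differing by .5 SD between two arms: .10 × .5 = .05 SD.

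Where the departure is unrelated to observed variables, the expected imputed minus complete-case difference is about 0 in all of these.

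**Behaviour of the trigger.** A simulation used N = 400 in the 2 × 2 design, three waves correlated .52, a true main effect of .4 SD and loss at 6 months only. It compared 20 imputations (using baseline, 3-month outcome and arm) with complete-case ANCOVA over 600 replicates. The missingness slope (logistic, 1.5 per SD) and the .05 SD cut-off for a difference are assumptions. Estimates, differences and bias are for 10% missing; CC is complete-case and MI is imputed.

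| Loss depends on | CC | MI | Mean MI − CC | Bias of MI | P(difference > .05 SD), 10% missing | Same, 20% missing |
|---|---|---|---|---|---|---|
| Nothing | .402 | .401 | −.001 | −.002 | .000 | .005 |
| 3-month outcome, both sides of the factor (ignorable) | .383 | .395 | +.012 | −.001 | .003 | .065 |
| 3-month outcome, intervention side only (ignorable) | .436 | .403 | −.033 | −.001 | .120 | .640 |
| Unexplained part of 6-month outcome, intervention side only | .524 | .523 | −.0003 | +.123 | .000 | .003 |
| 6-month outcome, both sides | .369 | .373 | +.003 | −.031 | .000 | .005 |
| 6-month outcome, intervention side only | .496 | .485 | −.010 | +.085 | .003 | .028 |
| 6-month outcome, opposite directions on the two sides | .585 | .565 | −.020 | +.162 | .008 | .198 |

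Across all scenarios, the correlation between the MI − CC difference and the bias of MI lay between −.03 and .18. If a difference is read instead as a change in significance at .017, the two analyses disagreed in at most 1.2% of replicates at 10% missing, in any scenario. Few disagreements are to be expected with a true effect this large.

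**The case against.** Several points on the other side have weight.

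- **The comparison is not wholly blind.** A reader might infer that the trigger can never detect non-ignorable loss. That goes too far. When such loss is correlated with observed variables, the two results separate slightly (−.010 to −.020 SD in the stronger 10% scenarios), and in the most extreme 20% scenario the cut-off was passed in about a fifth of replicates. Abstinence is measured at baseline and 3 months, with urine screens in month 1 as well, so relapse wholly unrelated to observed data is an extreme case. What stands is that the separation is small beside the bias and not specific to it.
- **Firing under ignorable loss is partly intended.** The conditional analysis covers systematic as well as non-ignorable missingness and compares conditions. Loss that depends on observed variables in one arm is arguably systematic, and an extra analysis does no harm. This stands, so the fault lies mainly in the rule's silence when it is needed.
- **Retention.** A reader might infer that controls, having no study phone, will be lost more often. The documents do not show this. Measurement process/data collection describes tracking procedures said to keep contact even with controls, and all four groups have the same office visits.
- **The simulation rests on chosen mechanisms and a chosen cut-off.** It shows how the rule can behave and does not forecast this trial. Its inflated estimates come from a different pattern of loss than the 15%/5% example.
- **A statistical analysis plan may exist.** One might infer that no check on ignorability is planned anywhere; the article alone cannot show that. The conditional rule is nevertheless stated in the article, so it is open to comment as it stands.

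**Conclusion.** The point holds as a fault in a stated decision rule. Agreement between imputed and complete-case results does not support ignorability, and the difference between them has no reliable or specific power to reveal outcome-dependent loss. It should not decide whether the non-ignorable analysis is run.

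Under the assumed 15/5/5/5% loss and a departure of .5 to 1.0 SD, the factorial contrasts carry .025 to .05 SD, roughly 6 to 12% of "a moderate effect size of Cohen’s *d* = .4". For the two main effects this is toward the null. A reader might carry the 12 to 25% figure over to the primary tests, but it belongs to control versus a single arm, and the analysis section makes pairwise tests follow-ups to a significant effect. Loss concentrated in relapsers on the intervention side would inflate the effect; at 10% missing, the one-sided scenarios gave about .09 to .12 SD.

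Severity is limited by the expected follow-up of 90% or more and by the tracking procedures. The change is worth making, but the point does not by itself put the trial's conclusions in doubt.

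**What to change.** Delete the condition at the start of the third step, so that a non-ignorable sensitivity analysis for days of abstinence is always run and reported. Either of two forms would do:

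- the latent variable framework already named, with the three contrasts re-estimated under it and not only a test of whether missingness differs by condition; or
- delta-adjusted imputation that allows different shifts by arm, reporting the shift at which each primary conclusion changes.

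Keep the complete-case analysis as descriptive. If the statistical analysis plan already contains such an analysis, aligning the published wording with it is enough.

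The cost is modest extra programming and one supplementary table. No new data are needed, and the sample size and primary tests do not change.

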### Randomization

Participants are randomly assigned to receive recovery support as usual (control), EMAs only, EMIs only, or combined EMAs + EMIs. Randomization uses urn randomization [62] with a base rate of 25% per condition stratified by participant characteristics (gender, race, age, recruitment cohort, level of comfort using a smartphone), pretreatment measures of the dependent variables (days of abstinence, HIV risk behaviors), and prerandomization treatment (level of care, length of stay, type of discharge) to increase the likelihood that participants are distributed similarly across conditions. Urn randomization adjusts the probability of assignment to a condition in ways that simultaneously minimize differences in multiple stratification variables [63, 64]. Only the research coordinator and protocol monitor responsible for scheduling, proficiency testing, and protocol supervision have access to information about who is in each condition. The research coordinator informs participants of their group assignment, describes the next steps, schedules training, and provides an appointment card for the next office visit.

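### The pairwise power is stated for stand-alone tests at .0083, but the plan gates those tests and still divides .05 by six; on its own inputs the procedure delivers about 67–75%, not at least 80%

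*Protocol article*

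**What the plan says.** **Sample size.** The effect size is "a moderate effect size of Cohen’s *d* = .4". The target for the arm-versus-arm tests is "at least 80% power for all six pairwise comparisons with a family wise alpha of < .0083", and the section reports this target as met: "275 per pair for H1 and H2) will be sufficient to have 80% power for a two-tailed test of" .0083. It presents these tests as the basis of the design: "we have powered this design for the most conservative pairwise tests so that we can look at the efficacy of each combination" relative to control and to each other. No condition on running them is mentioned.

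**Statistical analysis, analysis for aims 1 and 2.** Three contrasts (EMA or not, EMI or not, interaction) are tested on days of abstinence at .05/3 = .017. Then: "If there is a significant effect for H1 or H2, we will also examine all six of the possible pairwise comparisons". The declared experiment-wise error for the pairs is .05, and each pair is tested at .05/6 = .0083. The same section expects each component to work and the combination to bring an additional effect.

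**Aims and hypotheses.** H1 is worded as each of the three active groups compared with the control group.

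**The concern.** The two sections define success for a pairwise comparison differently. In the Sample size section a pair succeeds if its own test passes .0083. In the analysis section it must pass .0083 and one of the three contrasts must also be significant. Power for the first event overstates power for the second whenever the contrasts can all miss.

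The six-fold division also ignores what the gate already provides. Three contrasts at .05/3 form a 5% test that all four arms are equal. If the arms are not all equal, at most three of the six pairwise nulls can still be true (three arms equal, the fourth different). Dividing by three then suffices behind the gate.

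At stake are the comparisons with control in which H1 is worded. The contrasts average over the other factor and do not answer that question directly.

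**Working it through.** **Inputs.** d = .4, total n' = 549, 275 per pair, two-tailed tests and pairwise level .0083 are from Sample size. The base rate of 25% per arm is from Randomization. The .017 contrast level and the gate are from the analysis for aims 1 and 2. The 90% completion rate is already inside the 1120 observations.

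**1. Effective n.** 1120/(1 + .52 × 2) = 549, as stated. Per arm this is 549/4 ≈ 137; per pair 549/2 ≈ 275.

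**2. The stated pairwise power, no gate.**
- z = .4/√(2/137.5) = 3.317. The two-sided limit at .05/6 is 2.638.
- Power = Φ(3.317 − 2.638) = Φ(.678) ≈ 75%, not 80%.
- Reaching 80% needs about 304 per pair. With the unrounded d = LN(1.9)/1.65 = .389, power is 72.1%.
- At .05/3 the limit is 2.394, and power = Φ(.923) ≈ 82%.

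**3. How often the gate opens.** The contrasts are orthogonal, so with equal arms their estimates are independent. Each has standard error √(4/549) = .0854. A contrast of .4 is detected at .017 with probability Φ(4.686 − 2.394) = .989; a contrast of .2 with Φ(2.343 − 2.394) = .480. With arm means in the order control, EMA, EMI, EMA + EMI:
- (0, .4, .4, .8): both main effects are .4. Gate ≈ 1 − .011² ≈ 100%.
- (0, 0, 0, .4) or (0, .4, .4, .4): all three contrasts are .2 in size. Gate = 1 − .520³ = 85.9%.
- (0, .2, .2, .4): both main effects are .2, interaction 0. Gate = 1 − .520² × .983 = 73.4%.

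**4. Power of the planned procedure.** This is the probability that the gate opens and the pair passes, for a pair differing by .4, from 2,000,000 simulated sets of four arm means with n' = 549:

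| Arm means | No gate, .0083 | As written: gate and .0083 | Gate and .0167 |
|---|---|---|---|
| (0, .4, .4, .8), one component vs control | 75.0% | 75.0% | 82.1% |
| (0, 0, 0, .4), combined vs control | 75.0% | 71.0% | 75.8% |
| (0, .4, .4, .4), any active arm vs control | 75.0% | 71.0% | 75.8% |
| (0, .2, .2, .4), combined vs control | 75.0% | 67.5% | 70.3% |

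If the combination adds a positive interaction, as in (0, .4, .4, 1.2), the gate again opens about 100% of the time, and each component versus control keeps 75% as written.

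**5. Experiment-wise error over the true-null pairs, same simulation.**

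| Configuration | Gate and .0083 | Gate and .0167 |
|---|---|---|
| All four arms equal | 2.6% | 3.6% |
| Three arms equal | 2.3% | 4.4% |
| Two equal pairs | 1.7% | 3.3% |

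**The case against.** **The low figures are not what the plan expects.** A reader might infer that power falls to 67–71% under the plan's own expectations. The documents do not support that. The analysis section expects both components to work and the combination to add. At d = .4 per component, the gate then opens almost every time and costs nothing. The 67–71% range needs one active arm, three equal active arms (a negative interaction) or half-size component effects. H1 gives only directions against control and does not assume equal effects. This objection stands.

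**The gate is not the whole shortfall.** About 5 of the 9 to 13 points between 80% and 67–71% arise before any gate, because the stand-alone figure is 75%. The gate adds 0 to about 8 points. This also stands.

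**Nothing is invalid.** A reader might take the gate plus the six-fold correction as a statistical error, or conclude that the gate makes a pairwise correction unnecessary. Neither follows. Bonferroni behind a gate controls the declared error. Some correction is needed: unadjusted .05 tests behind the gate give about 12% error when three arms are equal. What is lost is efficiency.

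**The gate may be looser.** The wording can be read as letting either outcome open the pairwise tests, and .017 is stated only for days of abstinence. With contrasts at .05, gated power at .0083 returns to about 75% in all these patterns. That removes the gate's cost, but 75% is still short of 80%. A gate of three tests at .05 opens 1 − .95³ = 14.3% of the time when all arms are equal, so it would not justify .0167.

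**Stating single-test power is ordinary practice.** That is fair in general. Here, however, the document fixes both the gate and the level, and says the design was powered for these tests.

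**Conclusion.** The mismatch is real and of moderate size. As written, the procedure gives about 75% power for a .4 difference when both components work at d = .4 and the combination adds, about 71% when only the combined arm works or the active arms are equal, and about 67% for EMA + EMI versus control with half-size additive effects. None reaches the promised 80%. In the first pattern the .0083 level is the cause; in the others the gate adds to it. The procedure uses at most about 2.6% of the 5% error it declares, so this is a loss of efficiency and not a validity fault.

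The figures assume normal, equal-variance arm means, equal allocation, a gate on the days-of-abstinence contrasts at .017, and the plan's effective-n' method taken at face value. If only 100 independent persons per arm were counted, stand-alone power would be 57.5%.

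**What to change.** In the analysis for aims 1 and 2:
- **Days of abstinence.** Open the pairwise tests only if one of this outcome's own three contrasts is significant at .017. Then test all six pairs at .05/3 = .0167, citing Shaffer's bound.
- **HIV risk.** Use .0167 only if this outcome's own three contrasts are also gated at .017; otherwise keep .0083.

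In Sample size, replace the 80% with the power of the gated procedure under a stated pattern of arm means.

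**Gain.** Power becomes about 82%, 76% and 70% in the three patterns, with simulated experiment-wise error at most 4.4%.

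**Cost.** A few sentences and one restated figure, with no change to data or sample size. The HIV-risk contrasts face a stricter level if they serve as a gate, and the stated power will depend on the assumed pattern. The change does not recover everything: with half-size additive effects, dropping the gate and keeping .0083 would give 75% against 70%. If that pattern is thought likely, dropping the gate is the better choice.

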#### Mediation analysis (aim 3)

H1 and H2 will provide a test of the direct effects of randomization. To evaluate mediation (H3), we will evaluate (1) the extent to which a direct effect exists between days of abstinence in months 1 to 3 post enrollment and HIV risk behaviors in months 4 to 6 post enrollment (i.e., is the path coefficient significant?) and (2) the extent to which including days of abstinence eliminates or reduces the direct effect of the EMAs, EMIs, and EMAs + EMIs on HIV risk behaviors using the Preacher et al. [79] framework for testing mediation in MSEM with REML in MPlus. Note that to ensure temporal precedence, we have purposely set up random assignment at the time of enrollment, days of abstinence from months 1 to 3 post enrollment, and HIV risk behaviors in months 4 to 6 post enrollment. Loss of statistical significance in the direct path coefficient from the intervention conditions to the HIV risk behaviors would indicate full mediation; a reduction in the path coefficient would indicate partial mediation. The statistical significance of the reduction will be evaluated using MacKinnon’s [80] joint-significance testing of the path *z*-scores, with a Sobel test using a standard error based on bootstrapping and criteria of *p* < .05 on the degree of change. We expect the increased days of abstinence to be the primary mediator of change in HIV risk behaviors, consistent with data from our prior research [6, 7, 81, 82].

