## Methods/design

### Aims and hypotheses

The aims of this randomized controlled trial (RCT) are to (1) test the effect of EMAs, EMIs, and EMAs + EMIs on days of abstinence from alcohol and other drugs, (2) test the effect of EMAs, EMIs, and EMAs + EMIs on HIV risk behaviors, and (3) evaluate the extent to which changes in days of abstinence mediate the effect of EMAs, EMIs, and EMAs + EMIs on HIV risk behaviors. The primary hypothesis is that (H1) participants assigned to (H1a) EMAs, (H1b) EMIs, and (H1c) EMAs + EMIs will have, compared with control-group participants, more days of abstinence from drugs and alcohol in the 6 months post discharge from treatment. The two secondary hypotheses are that (H2) participants assigned to EMAs, EMIs, and EMAs + EMIs will have, compared with control-group participants, fewer HIV risk behaviors in the 6 months post discharge, and that (H3) days abstinent at 3 months post discharge will mediate the effects of EMAs, EMIs, and EMAs + EMIs on HIV risk behavior at 6 months post discharge.

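### The mediation rule takes a non-significant direct path as full mediation, so it would often label partial mediation as full; the non-randomised abstinence-to-HIV path also has no stated baseline adjustment

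*Protocol article*

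**What the plan says.** The Mediation analysis (aim 3) section of the protocol article gives two labelling rules. The first is "Loss of statistical significance in the direct path coefficient from the intervention conditions to the HIV risk behaviors would indicate full mediation". The second is that "a reduction in the path coefficient would indicate partial mediation". The change is then tested by joint significance of the path z-scores, "with a Sobel test using a standard error based on bootstrapping", at p < .05.

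The hypothesis (H3, Aims and hypotheses) is that days abstinent at 3 months "will mediate the effects of EMAs, EMIs, and EMAs + EMIs on HIV risk behavior at 6 months post discharge". For the path from abstinence in months 1 to 3 to HIV risk in months 4 to 6, the safeguard named is timing: "to ensure temporal precedence, we have purposely set up random assignment at the time of enrollment". The section lists no baseline covariate for that path.

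Baseline abstinence and baseline HIV risk do appear elsewhere. They are urn variables (Randomization). They feed a propensity score covariate (Analysis for aims 1 and 2), whose stated purpose is to reduce unexplained variance. They are also candidate moderators (Combined and additional analyses).

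**The concern.** Failing to reject a zero direct effect is not evidence that it is zero. The direct path is estimated with limited precision, and the rule turns that imprecision into a substantive conclusion. A coefficient that moves from p = .04 to p = .06 when the mediator is added would change the label while hardly changing the estimate. At stake is what aim 3 reports: that abstinence carries the whole effect of the apps on HIV risk, when close to half may act by another route.

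Separately, abstinence in months 1 to 3 is not randomised. Temporal order rules out reverse causation but not a stable personal trait that drives both abstinence and HIV risk. The article's ICCs of .52 and .51 show that both measures have a large stable component.

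**Working it through.** **Inputs.** From Sample size: N = 400, d = .4, ICCs .52 (abstinence) and .51 (HIV risk), indirect effect d = .22 with at least 90% power. From Missing data: 90% follow-up, so 360 analysed (180 v 180 for one factor).

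**The article's own figures first.**
- Effective n: 1120/(1 + .52 × 2) = 549 and 1120/(1 + .51 × 2) = 554, as stated.
- HIV-risk power at n' = 554, d = .4, two-sided .05: 99.7%, against 99% stated. So .4 is the size implied for HIV risk too.
- H3 power: the article does not split .22 into its two paths. Assuming a = .4 (arm to abstinence) and b = .22/.4 = .55 (abstinence to HIV risk, absolute value), at N = 360 the joint test has 96.7% power and the Sobel test 95.3%. Both agree with the stated figure.

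**1. The full-mediation label.**
- Direct effect: .40 − .22 = .18, which is .18/.40 = 45% of the total.
- Ignoring the variance that the mediator explains: SE = 2/√360 = .105, z = .18/.105 = 1.71, and P(not significant) = Φ(1.96 − 1.71) = 60%. The same sum gives 56% at N = 400 and 44% at n' = 554.
- Allowing for that variance: residual SD = √(1 − .55²) = .835. Correlation of arm with mediator has r² = .04/1.04 = .038, which inflates the SE by 1/√(1 − .038) = 1.02. SE = .105 × .835 × 1.02 = .090, z = .18/.090 = 2.0, and P(not significant) is about 48%.
- Simulation with the same scaling: 46% of trials with a significant total effect are labelled full. Among those that also pass joint significance it is 47%. Without the scaling, 53.9% of all trials get the label and 91.7% have a significant total effect, so the share is .539/.917 = 59%.
- With a total effect of d = .30, half of it mediated, the share is 59%.

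**2. Does the label rule create mediation from nothing?** With b = 0, no confounding and a true direct effect of .4, the label criterion is met in 1.1% of trials, and together with a passed joint test in 0.2%. It does not.

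**3. Confounding of the abstinence-to-HIV path.** Set the true b to 0, a = .4, and trait variances of .52 and .51. The trait correlation ρ is not in the documents and is varied.
- Spurious b = ρ × √(.52 × .51) = .515ρ, with SE about 1/√360 = .053.
- Power of the a path: Φ(.4/.105 − 1.96) = 97%.
- At ρ = −.2: |b| = .103, z = 1.95, P(significant) about .50; × .97 = 48%.
- At ρ = −.3: |b| = .154, z = 2.93, P(significant) about .83; × .97 = 81%.

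Simulated share of trials in which the joint test declares mediation:

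| Assumed ρ | No baselines | Both baselines in both equations |
|---|---|---|
| 0 | about 5% | about 5% |
| −.1 | about 17% | about 7% |
| −.2 | about 47% | about 9% |
| −.3 | about 81% | about 16% |
| −.5 | about 96% | about 38% |

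Repeat runs differ by one to three percentage points. Baseline adjustment does not restore 5%, because each baseline is a single noisy measure of the trait.

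**The case against.** The strongest reply is that the full/partial sentence only names a result, and that the next sentence tests it formally. This stands against one tempting inference, that the loss-of-significance rule lets H3 be declared when it is false. The documents do not support that, because joint significance and a Sobel test are also required, and step 2 gives 0.2%. The reply does not rescue the label. Joint significance asks whether an indirect effect exists, not whether the direct effect is absent, and the mislabelling rate is no lower among trials that pass it.

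A reader might also infer that the plan makes no use of baseline values. That is too flat, since they enter the propensity covariate. That covariate is described under aims 1 and 2, however, and its weights are chosen to predict arm. It is not presented as control of mediator-outcome confounding and cannot be relied on for it. It is also fair that a condensed article may leave the H3 covariate list to the analysis plan, so this part is secondary.

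The Sobel test might look like a further error, because it treats a product of coefficients as normal. It is the stricter of the two tests listed. With b = 0 and no confounding it declares mediation in 1.9% of simulated trials (using a delta-method SE), against 4.3% for joint significance. Dropping it would be a preference.

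Finally, the calculations use single-level regressions for one two-level factor, not the planned multilevel structural equation model. That is correct, and the percentages are indicative.

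**Conclusion.** The stated rule is wrong as written. On the article's own effect sizes it would label about 45% of trials with a significant total effect as full mediation when 45% of the effect is direct. This rests on a total HIV-risk effect of d = .4, an indirect effect of .22 (given as the size the test is powered for, not as a forecast), a = .4 and b = .55, and N = 360. The share is higher, 59%, for a total of d = .30 split evenly. The error is one of labelling; H1 and H2 are untouched.

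The confounding point is real but secondary. Its size depends wholly on an assumed trait correlation: no inflation at 0, and a large excess of false declarations by −.2 to −.3. Nothing in the documents fixes that value, and nothing rules out further covariates in a fuller plan.

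**What to change.** - Delete the full/partial rule. Report the indirect effect, the direct effect and the proportion mediated, each with a bootstrap confidence interval, and base the H3 claim on the indirect effect only.
- Enter baseline days of abstinence and baseline HIV risk directly in both path equations (arm to abstinence, and abstinence to HIV risk), and state that residual mediator-outcome confounding remains.

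The cost is wording. Both baselines are already collected with the GAIN-Q3, and the bootstrap is already planned. The downside is a more modest mediation claim.
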